#### Aim 2: Analytic plan

We will use model-based causal mediation analysis (CMA) [55] to evaluate whether changes in sense of meaning in life (LAP-R PMI) immediately posttreatment (T2) mediate the effect of treatment arm on benefit finding (BFS), anxiety (HADS-A), and depression (HADS-D) at 6-month follow-up. We will use the *mediation* [56] package in R [57] to conduct mediation analyses for each of the three outcomes (BFS, HADS-A, HADS-D). Each mediation analysis will estimate the average causal mediation effect (ACME, the effect of the treatment arm on the outcome via the mediator), average direct effect (ADE, effect of treatment arm on the outcome measure excluding the mediation), the average total effect (ATE, sum of the ACME and ATE), and the proportion of the ATE mediated by the mediator variable (ACME/ATE). To estimate these effects, we will input two models, (1) a mediator model and (2) an outcome model, to the estimation functions in the *mediation*R package. The (1) mediator model will be a linear regression with T2 LAP-R PMI as the dependent variable and treatment arm and baseline (T1) LAP-R PMI as independent variables, controlling for baseline outcome measure (e.g., T1 BFS) and study site (randomization stratification variable). The (2) outcome model will be a linear regression with the T3 outcome measure (e.g., BFS) as the dependent variable and treatment arm, baseline outcome measure, T2 and T1 LAP-R PMI, and study site (randomization stratification variable) as independent variables. We will conduct these mediation analyses once excluding those participants with missing data for any variables in the model, and we will conduct sensitivity analyses replicating the model after applying multiple imputation of missing data using chained equation analyses [58]. Other sensitivity analyses will be conducted to evaluate results testing the impact of unmeasured pre-treatment confounding variables [59].

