## Data collection and management

### Plans for assessment and collection of outcomes {18a}

Data will be collected via self-report measures using the Research Electronic Data Capture (REDCap), a secure web application for creating and managing online survey databases. The Clinical Research Coordinator (CRC)—who receives training in data quality assurance—will send all study assessments to participants at the appropriate timepoint. Outcomes will be measured at four time points: baseline, directly after informed consent or until consent expiration (i.e., 45 days; T1), immediately post-intervention + 2 weeks (T2), 6-month follow-up ± 4 weeks (T3), and 12-month follow-up ± 8 weeks (T4). This will allow flexibility for study assessment completion and aid caregiver retention throughout the entire study. All data collection forms can be found in the study protocol.

At baseline (T1), participants will complete demographic information (e.g., age, sex, race, ethnicity, income), caregiver characteristics (e.g., relationship to the patient, length of caregiving), and a survey about psychosocial service use, preferences, and perceived barriers, using established questionnaires from our group’s previous studies. Participants will also complete all outcome measures (i.e., sense of meaning in life, spiritual well-being, anxiety and depression, benefit finding, meaning in caregiving, caregiver burden, and social support) at T1. At T2, in addition to study outcome measures, participants will complete the Credibility and Expectancy Questionnaire (CEQ) to assess treatment acceptability and perceived effectiveness. Pre-loss (preparedness for patient death, pre-loss grief intensity, risk for bereavement mental health challenges, engagement in advance care planning) and post-loss (the presence of regret, unfinished business, post-loss grief intensity, risk for post-loss bereavement mental health challenges, and occurrence of advance care planning discussions and goal-concordant care at patients’ end of life) bereavement outcomes will also be explored at all timepoints.

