## Statistical methods

### Statistical methods for primary and secondary outcomes {20a}

Descriptive statistics will be calculated for baseline demographic and caregiver clinical variables, summarizing each outcome by treatment arm. We will assess the distribution of each study outcome and, if necessary, perform corrective transformations before calculating inferential statistics. We will also perform all efficacy analyses by the intention-to-treat principle, meaning that all randomized participants will be analyzed regardless of dropout or treatment adherence in their respective study arm. All endpoint comparisons between study arms will be adjusted for the randomization stratification variable (study site).

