### Methods in analysis to handle protocol nonadherence and any statistical methods to handle missing data {20c}

Efforts to minimize missing data include ensuring an efficient and organized trial design, robust training of research staff, and reducing participant burden by utilizing remote study assessments rather than in-person visits. For participants who report time constraints or difficulty completing study assessments, we will ask them to only complete primary outcome measures (LAP-R and FACIT SWBS) in order to minimize missing data regarding primary study aims. Missing data will be treated using sensitivity analyses and other data analytic approaches that are responsive to missingness. Specifically, we will first examine whether data missingness is associated with variables such as randomization arm and baseline outcome measures by comparing caregivers with complete data to those with missing data. If data is not missing at random, then we will modify analyses by controlling for factors associated with data missingness [60, 61].

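### Aim 2 mediation models leave out mediator-outcome confounders already collected at baseline, and the main analysis uses complete cases although imputation is already planned

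*Protocol article*

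**What the plan says.** In the protocol article, Aim 2: Analytic plan, each mediation analysis uses two linear regressions. The mediator model has T2 PMI as dependent variable, with "treatment arm and baseline (T1) LAP-R PMI as independent variables, controlling for baseline outcome measure (e.g., T1 BFS) and study site". The outcome model has the T3 outcome (BFS, HADS-A or HADS-D) as dependent variable, with arm, the T1 outcome, T1 and T2 PMI, and site. No other baseline variable is named.

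On missing data: "We will conduct these mediation analyses once excluding those participants with missing data for any variables in the model". Imputation comes second: "we will conduct sensitivity analyses replicating the model after applying multiple imputation of missing data using chained equation analyses". On confounding: "Other sensitivity analyses will be conducted to evaluate results testing the impact of unmeasured pre-treatment confounding variables".

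Two other places bear on this. Section {18a} states that at T1 "participants will complete demographic information (e.g., age, sex, race, ethnicity, income), caregiver characteristics" and all outcome measures, so spiritual well-being, both HADS subscales, burden and social support are also available at baseline. Section {20c} says of caregivers short of time that "we will ask them to only complete primary outcome measures (LAP-R and FACIT SWBS".

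The total effect is described as "the average total effect (ATE, sum of the ACME and ATE".

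**The concern.** Randomization protects the effect of arm on T2 PMI and on the T3 outcome. It does not protect the path from T2 PMI to the T3 outcome, because caregivers are not randomized to a level of meaning. That path has a causal reading only if the common causes of the two variables are adjusted for. Baseline spiritual well-being, burden, support, the other HADS subscale, age, sex and relationship to the patient are plausible common causes. All are planned T1 measurements, yet they appear in neither model.

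The second issue is who is analysed. Suppose a caregiver gives T2 PMI but has no T3 outcome. Complete-case analysis removes that caregiver from the mediator model too, although all the data that model needs are present. If T3 missingness depends on T2 PMI, this selects on the mediator model's own dependent variable. The data are then still missing at random, the assumption that Aim 1: Analytic plan calls reasonable and uses to justify a method that keeps participants with missing follow-up. The short battery in {20c} can create this pattern when used at T3, since it keeps LAP-R and drops BFS and HADS.

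At stake is the size of the mediated effect and the proportion mediated, which carry the mechanism claim of a secondary objective. The Aim 1 efficacy conclusion is not affected.

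**Working it through.** **Inputs from the protocol article.** N = 200, 100 per arm; 20% attrition by T2; baseline to follow-up correlation 0.5; two-sided type 1 error 0.025 per endpoint; 80% power; detectable difference 0.48 SD (Sample size {14}). There is no power or precision figure for Aim 2, no T3 attrition rate and no correlation among the measures. Everything else below is assumed.

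**1. The plan's own figure.** A mixed model with separate baseline means, 100 per arm at T1 and 80 at T2, gives 3.083 × √(2 × [(1 − 0.5²)/80 + (1 − 0.5)²/100]) = 3.083 × √0.02375 = 0.475, which rounds to 0.48. The figure reproduces. It serves below only as an illustrative arm-to-mediator effect.

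**2. Confounding, product rule.** Let an omitted T1 variable have partial correlation r with both T2 PMI and the T3 outcome, given the covariates already in the models. It adds about r × r to their partial correlation. This is exact when the true value is 0. For a true value of 0.30 (assumed), the exact expression is 0.30 × (1 − r²) + r².

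| r (assumed) | r² | r² / 0.30 | Exact value, true 0.30 |
|---|---|---|---|
| 0.1 | 0.01 | 3% | 0.297 + 0.01 = 0.307 |
| 0.2 | 0.04 | 13% | 0.288 + 0.04 = 0.328 |
| 0.3 | 0.09 | 30% | 0.273 + 0.09 = 0.363 |

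The product rule is therefore the upper reading. At a true value of 0.30 the exact increments are 0.007, 0.028 and 0.063.

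**3. Confounding, effect on the ACME.** A large-sample simulation (400,000 records, no missing data) fitted the two planned models without site. Assumed: arm-to-mediator effect 0.48, mediator-to-outcome coefficient 0.30, direct effect 0.10, so the true ACME is 0.48 × 0.30 = 0.144. An omitted baseline variable had coefficient u on both T2 PMI and the T3 outcome. The residual variance of T2 PMI is 0.75, so the fitted mediator coefficient should be 0.30 + u²/0.75.

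| u (assumed) | 0.30 + u²/0.75 | Simulated ACME | Change from 0.144 |
|---|---|---|---|
| 0.2 | 0.353 | 0.171 | +19% |
| 0.3 | 0.420 | 0.203 | +41% |
| 0.4 | 0.513 | 0.246 | +71% |

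Adjusting for the variable returned 0.143 to 0.145. These are stronger confounders than those in step 2: u = 0.2 is already a correlation of 0.2/√0.75 = 0.23 with T2 PMI given the modelled variables. At u = 0.1 the formula gives 0.30 + 0.01/0.75 = 0.313, about +4%.

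**4. Complete cases, bias.** Same model, no omitted confounder, 80% or 65% of caregivers kept:

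| Missingness depends on | ACME at 80% / 65% kept | Change from 0.144 |
|---|---|---|
| Arm and T1 PMI | 0.144 / 0.144 | none |
| T2 PMI, both arms | 0.136 / 0.134 | −6% / −7% |
| T2 PMI, both arms, stronger | 0.129 / 0.125 | −10% / −13% |
| T2 PMI, SP-C only | 0.102 / 0.074 | −29% / −49% |

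In the three T2 PMI scenarios the mediator-to-outcome coefficient stayed at about 0.30; the loss was in the arm-to-mediator effect. Estimating that effect from every observed T2 PMI returned 0.144 to 0.146.

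**5. Complete cases, precision.** With the planned attrition, 200 × 0.80 = 160 have T2 PMI. If 25% to 40% lack some model variable (assumed), 150 to 120 remain. The standard error of the arm-to-mediator effect grows by √(160/150) = 1.03 to √(160/120) = 1.15. The mediator-to-outcome path gains little from imputation, because caregivers without a T3 outcome carry little information on it.

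**The case against.** The strongest reply is that the plan already deals with both issues. Imputed results will be reported beside complete-case results, so a divergence would show. An unmeasured-confounding sensitivity analysis is planned. The models already contain the baseline versions of mediator and outcome, usually the most important confounders. Section {20c} also allows control for factors associated with missingness, which could bring in further covariates.

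Much of this stands. The adjustment already present means that only residual confounding matters, and the documents give no figure for it. The larger selection losses need dropout that depends on PMI in one arm only, which nothing in the documents indicates. What does not stand is that the planned steps remove the problem. A sensitivity analysis for unmeasured confounders gauges robustness; it does not adjust for variables that were measured. The {20c} rule is data-driven and aimed at missingness, not at common causes of PMI and the outcome. Showing two missing-data results does not settle which one carries the conclusion.

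A reader might also infer that complete cases contradict the intention-to-treat statement in {20a} that "all randomized participants will be analyzed regardless of dropout or treatment adherence". That sentence is about efficacy analyses. Aim 2 is a secondary mechanism objective, so the documents do not support a contradiction.

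**Conclusion.** The point holds in a conditional form. Measured, plausible mediator-outcome confounders are left out of both models, and any residual confounding by them biases the ACME, upward if they act in the same direction on both variables. The size is unknown: by the product rule, 0.01, 0.04 or 0.09 on the partial correlation for assumed residual correlations of 0.1, 0.2 or 0.3. The complete-case analysis is unbiased if missingness depends only on arm and modelled baseline variables. If T3 missingness depends on observed T2 PMI, it can be biased where a suitable imputation is not. In the scenarios run the bias was downward, but losing low scorers mainly from MCP-C would push the other way.

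A reader might infer that mediation will be overstated. The documents do not support a net direction: the two mechanisms may offset each other, and neither is certain to operate. Nor does the circular definition of the total effect threaten a result. The same sentence names the direct effect, and the named R package computes the total correctly, so this is an erratum.

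**What to change.** 1. Prespecify in both models a short list of T1 covariates already collected, for example SWBS, HADS-A, HADS-D, CRA, FSSQ, age, sex and relationship to the patient.
2. Make the multiple-imputation analysis the main one. Impute by arm and include observed T2 PMI and SWBS in the imputation model, so that short-battery caregivers contribute. Report complete cases as sensitivity. The two changes belong together, because extra covariates under case deletion could exclude more people.
3. As an erratum, define the total effect as ACME + ADE.

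No new data are needed and imputation is already planned, so the cost is analysis-plan wording and some computing. The downsides are a few degrees of freedom and dependence on the imputation model, including its missing-at-random assumption. Baseline covariates will not remove post-randomization confounding, such as bereavement before T2; the report should say so.

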#### Aim 3: Analytic plan

Based on our group’s prior research, we estimate that approximately 50 (25%) participants in this study will become bereaved by the 12-month follow-up assessment (T4). Among the subset of non-bereaved caregivers, we will utilize the same cLMM analysis used in assessing the secondary outcomes in Aim 1 to examine differences between study arms in risk for bereavement mental health challenges (BRISQ-P) and pre-loss grief (PG-12-R). Multinomial logistic regression analyses will assess between-arm differences in T4 preparedness for loss in this subset, controlling for study site and baseline preparedness for loss. Among the subset of caregivers who become bereaved by T4, we will assess between-arm differences in T4 risk for bereavement mental health challenges (BRISQ-B), post-loss grief (PG-13-R), and the presence of regret (single item, yes/no) using linear (BRISQ-B, PG-13-R) and logistic (presence of regret) regression models controlling for study site and time since bereavement. Also, among those bereaved before T4, we will test whether higher posttreatment (T2) preparedness for patient death and/or engagement in ACP discussions (ACP Execution Checklist score) are associated with lower levels of T4 post-loss grief (PG-13-R) by fitting linear regression models predicting T4 PG-13-R scores. These models will control for study site, time since bereavement, and treatment arm, and they will include either T2 preparedness for patient death or the ACP Execution Checklist score as the focal predictor.

### Interim analyses {21b}

Not applicable.

### Methods for additional analyses (e.g., subgroup analyses) {20b}

All detailed analyses comparing study arms (MCP-C versus SP-C) will be adjusted for randomization stratification variable (study site).

### Methods in analysis to handle protocol nonadherence and any statistical methods to handle missing data {20c}

Efforts to minimize missing data include ensuring an efficient and organized trial design, robust training of research staff, and reducing participant burden by utilizing remote study assessments rather than in-person visits. For participants who report time constraints or difficulty completing study assessments, we will ask them to only complete primary outcome measures (LAP-R and FACIT SWBS) in order to minimize missing data regarding primary study aims. Missing data will be treated using sensitivity analyses and other data analytic approaches that are responsive to missingness. Specifically, we will first examine whether data missingness is associated with variables such as randomization arm and baseline outcome measures by comparing caregivers with complete data to those with missing data. If data is not missing at random, then we will modify analyses by controlling for factors associated with data missingness [60, 61].

### Plans to give access to the full protocol, participant-level data, and statistical code {31c}

Reasonable requests for the study protocol or de-identified data can be made to the principal investigator.

## Oversight and monitoring

### Composition of the coordinating center and trial steering committee {5d}

The study team at the coordinating center, ISMMS, is comprised of the CRC and study principal investigator. Co-investigators are housed at MSK and SCCC. The study team at the coordinating site meets weekly to discuss recruitment, active participants, and study questionnaire completion updates. There is no trial steering committee for the current study.

### Composition of the data monitoring committee and its role and reporting structure {21a}

ISMMS/Tisch Cancer Institute (TCI) is serving as the IRB of record, and as such, the data and safety monitoring plan is standard to clinical trials completed at TCI. The TCI Data and Safety Monitoring (DSM) plan ensures that all clinical trials are high quality, routinely monitored, and meet sponsor, institutional, and governmental requirements. The plan includes all required elements of the DSM as defined by the NIH and the NCI: monitoring responsibilities, description of what is to be monitored (e.g., data types), frequency of reviews, protocol compliance auditing procedures, adverse event reporting procedures, suspensions of clinical research, and conflicts of interest.

A formal Data and Safety Monitoring Committee (DSMC), independent of the sponsor, was established in 2008 to ensure that all clinical trials that are greater than minimal risk at TCI have adequate data and safety monitoring plans. Interventional and institutional studies, Investigator-Initiated Trials (IIT) requesting that the TCI DSMC serve as the independent Data and Safety Monitoring Board—as is the case with the current investigation—undergo review of the protocol and Data and Safety Monitoring Charter prior to review by the Protocol Review and Monitoring Committee (PRMC) review. The PRMC is charged with the review of all new cancer-related clinical research protocols at Mount Sinai to assess their scientific merit and prioritize them relative to the mission and scope of the TCI. The PRMC coordinator submits the protocol and charter to the DSMC for pre-review. The DSMC Chair, in coordination with the DSMC Administrator, assigns each initial review to a physician and a biostatistician based on the member’s disease specialty and accounting for conflicts of interest. The protocol is submitted before a monthly DSMC meeting, and questions for the PI and responses are documented in minutes. Protocol review includes a plan of review for each arm, dose level or stratum including the number of participants, predefined toxicities, dose adjustments, reporting structures for unanticipated problems and serious adverse events, response assessments, timing of reviews, dose-limiting toxicities, dose escalation rules, stopping criteria of the trial for toxicity or efficacy, and criteria defining maximum tolerated dose. Approval of the monitoring plan and charter is required before PRMC approval and is reviewed annually.

Further details are available in the TCI DSMC Charter.

### Adverse event reporting and harms {22}

There are no physical risks or side effects associated with participation in this study. Psychological risks are limited to possible distress related to engaging in a psychotherapy focused on the existential distress that arises from taking care of a patient with an advanced cancer. We will inform potential participants that it is reasonable not to participate if they feel discomfort in completing the assessment questionnaires or psychotherapy sessions. We will present questionnaires in a sequence that is sensitive to their recollection and thought about their experience of caregiving. All research staff will be trained to identify signs of psychological discomfort in participants, and participants reporting significant distress, including moderate depressive symptomatology (identified via the Hospital Anxiety and Depression Scale (HADS)) or suicidal ideation, will be referred to the in-house licensed clinical psychologist at MSK ([name]) and SCCC ([name]) or covering psychologist or psychiatrist on call, who will provide immediate evaluation, support, and/or referral as needed.

This is a minimal risk study, and we will only report serious adverse events (SAEs) including deaths that are believed to be at least possibly related to the study intervention or participation. An adverse event is considered any of the following: death, a life-threatening adverse event, an adverse event that results in inpatient hospitalization or prolongation of an existing hospitalization, a persistent or significant incapacity or disruption to the ability to conduct normal life functions, a congenital anomaly/birth defect, and other important medical events that may not result in the above events but may jeopardize the patient or participant based on medical judgment and may require medical or surgical intervention to prevent one of the outcomes mentioned above.

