#### Description of study measures

##### Screening and non-outcome measures

Caregiving-related distress: A modified version of the Distress Thermometer (DT) [32] will be used to screen for distress related to caregiving. Participants are asked to rate their distress on a scale of 0–10 (cutoff score ≥ 4) and indicate that their distress is related to caregiving to be eligible for the study. The distress thermometer will be administered at screening only.Treatment acceptability and perceived effectiveness: The Credibility and Expectancy Questionnaire (CEQ) is a 6-item measure of treatment acceptability and perceived effectiveness [33, 34]. This measure has been used extensively in prior research and has strong psychometric properties [34]. The CEQ is administered at T2 only.

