##### Secondary outcomes

Anxiety and depressive symptoms: The Hospital Anxiety and Depression Scale (HADS) is a 14-item measure of anxiety and depressive symptoms with items rated on a 0 to 3 scale, with higher scores indicating greater symptomatology. Scoring the HADS yields anxiety (HADS-A) and depression (HADS-D) subscale scores, each consisting of seven items. The HADS subscales have demonstrated strong internal consistency in cancer caregiver populations (Cronbach’s α range: 0.82–0.92) [26, 37]. The HADS is administered at T1–T4. Sense of meaning and purpose in caregiving: The Attitudes Toward Caregiving Scale (ATCS) [38] is a 43-item measure rated on a 5-point Likert-type scale that examines the extent to which caregivers find meaning in caregiving. Scores can be summed for a total score in addition to three subscales: loss/powerlessness, provisional meaning, and ultimate meaning, with higher scores indicating higher overall meaning and purpose. The ATCS is administered at T1–T4 in non-bereaved caregivers.Benefit finding: The Benefit Finding Scale (BFS) is a 17-item measure of perceived benefit finding that has been modified for caregiver populations. It has been used in our group’s previous research and has demonstrated strong internal consistency (Cronbach’s α range: 0.91 to 0.95 [39, 40]. The BFS is administered at T1–T4. Caregiver burden: The Caregiver Reaction Assessment (CRA) is a 24-item measure with items scored on a 5-point Likert-type scale [41]. Items are summed for a total score (range: 24–120) across five subscales: self-esteem, family support, impact on finances, schedule, and health. The CRA is a widely used measure of caregiver burden that has demonstrated good internal consistency and construct validity [42]. The CRA is administered at T1–T4 in non-bereaved caregivers.Social support: The Duke-UNC Functional Social Support Questionnaire (FSSQ) is an 8-item measure of perceived social support. Items are summed to a total score ranging from 0 to 40, with higher scores indicating greater perceived social support. The FSSQ has demonstrated strong internal consistency (Cronbach’s α = 0.94) [43]. The FSSQ will be administered at T1–T4.

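### The harms section defines an adverse event by seriousness criteria and reports only related serious events, so non-serious therapy-related distress, the one risk it names, is not reported as a harm

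*Protocol article*

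**What the plan says.** Three statements in the protocol article, section Adverse event reporting and harms {22}, bear on this.

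- The named risk. Physical risks are said to be absent, and "Psychological risks are limited to possible distress related to engaging in a psychotherapy focused on the existential distress".
- The reporting rule. On the ground that the study is of minimal risk, "we will only report serious adverse events (SAEs) including deaths that are believed to be at least possibly related to the study intervention" or participation.
- The definition. "An adverse event is considered any of the following: death, a life-threatening adverse event". The list goes on to hospitalization, "a persistent or significant incapacity or disruption to the ability to conduct normal life functions", congenital anomaly, and "other important medical events that may not result in the above events but may jeopardize the patient or participant based on medical judgment".

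The same section sets out what happens when distress is detected: "participants reporting significant distress, including moderate depressive symptomatology (identified via the Hospital Anxiety and Depression Scale (HADS)) or suicidal ideation, will be referred" to a psychologist or the psychiatrist on call. It does not say that these referrals are logged as adverse events or counted by arm.

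Elsewhere, the section on study measures says of the screening instrument that "The distress thermometer will be administered at screening only", and of the anxiety and depression scale that "The HADS is administered at T1–T4". HADS-A and HADS-D are secondary outcomes. Outcomes {12} and the Aim 1 analytic plan compare them between arms as model-estimated differences in mean change, with 95% confidence intervals.

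**The concern.** The list given for an adverse event is the usual list of seriousness criteria. It is also circular, because it uses the term it defines, and it leaves no class for a non-serious event. Combined with the reporting rule, this excludes the ordinary form of the only harm the plan expects. A caregiver who becomes markedly more distressed during existential work, and is referred for it, does not have an adverse event under this wording unless a seriousness criterion is met. Even then the event is reported only if judged possibly related. Participants and interventionists know the arm (Who will be blinded {17a}), and the article does not say who makes that judgment.

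The trial compares two active psychotherapies, one of which deliberately takes up existential themes, including the care partner's possible death. Whether that leaves more individual caregivers worse off than supportive therapy does is a reasonable question for its final report. The stated reporting rule would not answer it.

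**Working it through.** The main check is textual. The arithmetic at the end shows only what a count by arm could deliver.

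**1. The rule set against the named risk.** Therapy-related distress falls into three classes under section {22}.

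- Distress that leads to hospitalization, marked incapacity or an important medical event, and is judged possibly related: reportable.
- Distress that meets one of those criteria but is judged unrelated: not reportable.
- Distress that meets none of them, including distress that triggers a referral: outside the definition and not reportable, even if the therapy caused it.

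**2. Whether another part of the plan covers the third class.**

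- The Distress Thermometer is used only at screening, so it cannot show change.
- HADS is collected at all four time points and compared by arm, but the stated parameter is a difference in mean change. An unchanged mean is compatible with some participants improving and others deteriorating.
- Suicidal ideation is named as a referral reason separate from the HADS trigger, so HADS scores alone would not count it.
- Section {20c} lets participants with time constraints or difficulty complete only the LAP-R and the FACIT SWBS. HADS may therefore be missing for some of those who are struggling.

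**3. When events arise.** Under Participant timeline {13}, T1 is completed before randomization. HADS is given at T1 to caregivers selected for distress of 4 or more, so a referral prompted by T1 scores cannot be an effect of either arm. The Aim 3 plan expects about 50 participants (25%) to be bereaved by T4, so later distress may also reflect loss.

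**4. What a count could show.** The documents give no rate of referral or worsening. As an assumption, take rates of 10% and 20%. The half-width of the 95% interval for a difference in proportions is 1.96 × √[p₁(1−p₁)/n + p₂(1−p₂)/n].

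With n = 100 per arm (Sample size {14}):

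- 10% in both arms: 1.96 × √(0.0009 + 0.0009) = 1.96 × 0.0424 = 8.3 points.
- 20% in both arms: 1.96 × √(0.0016 + 0.0016) = 1.96 × 0.0566 = 11.1 points.
- 20% versus 10%: 1.96 × √(0.0016 + 0.0009) = 1.96 × 0.05 = 9.8 points, so a difference of 10 points has an interval of about 0 to 20.

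For HADS-based counts at T2, the plan's 20% attrition leaves 100 × 0.8 = 80 per arm. The same three cases give 9.3, 12.4 and 11.0 points.

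For comparison, zero related serious events among 100 participants in an arm gives an exact two-sided 95% upper limit of 1 − 0.025^(1/100) = 3.6% for that rate. It carries no information on non-serious distress.

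**The case against.** The strongest reply has four parts.

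- **A dropped word.** The preceding sentence is about serious adverse events, so the definition may simply lack the word serious. Restoring it would also remove the circularity. This is plausible, but it does not repair the reporting rule, which expressly covers only related serious events.
- **Escalation, not publication.** The rule may govern only what is sent to oversight bodies. Section {21a} attributes adverse event reporting procedures to an institutional data and safety monitoring plan and points to a charter, neither of which is shown. They may require more. This stands as a limit on the point. Even so, the article's own sentence is explicit, and if those documents say more, the texts need to be reconciled.
- **Distress is already measured.** HADS is compared by arm, and individual scores are held, so counts of participants who worsen could be derived. This also stands. It makes the remedy cheap, but the article does not plan such a count.
- **Referrals are an imperfect measure.** They depend partly on staff noticing distress in an unblinded trial, and they mix therapy effects with baseline distress and bereavement. This is correct, and the remedy has to allow for it.

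A reader might infer that distress can never appear among the reported harms. The documents do not support that, because the criteria for hospitalization, incapacity and important medical events are not confined to physical events. A reader might also infer that a planned harms comparison is defective. The article describes no such comparison, and its absence from a condensed article is not itself an error.

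**Conclusion.** The point holds in a limited form. Section {22} gives the definition of a serious adverse event under the name of an adverse event and confines reporting to related serious events. As written, non-serious therapy-related distress, the only risk the plan names, is not reported as a harm. No count of referrals by arm is stated, and the planned HADS comparison of means does not show how many individuals worsened.

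This is a weakness in safety reporting of moderate weight. The primary efficacy analysis is untouched. The amount of harm that would go unreported cannot be estimated from the documents, and the 10% and 20% rates above are assumptions used only to show precision. The conclusion rests on reading section {22} literally and on the unseen monitoring plan and charter not already requiring wider recording.

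**What to change.** 1. Relabel the list in section {22} as the definition of a serious adverse event, state separately what counts as an adverse event, and reconcile both with the data and safety monitoring plan and charter.
2. Tabulate by arm, for all randomized participants and whatever the judged relatedness, all serious adverse events and all referrals for distress, for the HADS trigger or for suicidal ideation that arise after randomization. Keep T1 referrals separate and show bereavement status.
3. Because referrals depend partly on unblinded staff, also give the number per arm who reach the existing HADS referral trigger at T2, T3 and T4, with the number who completed HADS as denominator. These data are already collected.

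The cost is revised wording, slight extra record-keeping and one table. No assessment is added, and neither the referral procedure nor the primary analysis changes. Recruitment is expected to run to March 2028 (Trial status), so prospective counting can still begin for much of the trial.
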